## Abstract

**Background:**

The prevalence of childhood obesity is increasing at a high rate in Brazil, making prevention a health priority. Schools are the central focus of interventions aiming the prevention and treatment of childhood obesity, however, randomized trials and cohort studies have not yet provided clear evidence of strategies to reduce prevalence of obesity.

The aim of this study is to present a protocol to evaluate the efficacy of combining school and household level interventions to reduce excessive weight gain among students.

**Methods:**

The intervention target fifth and sixth graders from 18 public schools (9 interventions and 9 controls) in the municipality of Duque de Caxias, metropolitan area of Rio de Janeiro, Brazil. A sample size of 2500 students will be evaluated at school for their weight status and those from the intervention group who are overweight or obese will be followed monthly at home by community health agents. Demographic, socioeconomic, anthropometric, eating behavior and food consumption data will be collected at school using a standardized questionnaire programmed in personal digital assistant. At school, all students from the intervention group will be encouraged to change eating habits and food consumption and to increase physical activity and reducing sedentary behavior.

**Discussion:**

This study will provide evidence whether integration of school with primary health care can prevent excessive weight gain among adolescents. Positive results will inform a sustainable strategy to be disseminated in the health care system in Brazil.

**Trial registration:**

ClinicalTrials.gov, NCT02711488. Date of registration: March 11, 2016.

## Background

The increasing prevalence of obesity in low and middle-income countries [1] requires tailored well-tested preventive strategies to curb the obesity epidemic. In Brazil, children and adolescents had the highest increase in the prevalence of obesity in the last decade [2], particularly in urban low-income areas, which concentrates high percentage of the Brazilian population [3, 4].

Usually, schools are the central focus of interventions aiming prevention and treatment of childhood obesity [5], however, randomized trials and cohort studies have not yet provided clear evidence of strategies to reduce the prevalence of obesity, according to a position paper of the of the U.S. Academy of Nutrition and Dietetics [5]. Potential limitations in these studies include heterogeneity of participants in cluster-randomized trials, baseline imbalance, underestimated sample size and overestimation of possible changes in body mass index [6].

We have been studying prevention of obesity in schools for many years and our studies published from 2008 to 2013 [7–10] have tested various activities for primary prevention. The PAAPPAS study, which stands for “parents, health care agents, students, and teachers for healthy eating” is a school-based randomized research project in its fourth version. In the first initiative, the main intervention focused on the reduction of sodas [7]. The second study was conducted among school cooks [8, 9] with the main aim of reducing use of sugar at school and also to reduce sugar intake and increase physical exercise among the school cooks. The third study, focused on positive messages to increase the intake of water, fruit, and beans and to reduce intake of cookies, sugar-sweetened beverages, and savory snacks [10]. The results of these studies, as well as, many the school-based initiatives based on primary prevention have been promising regarding the modification of behaviors associated with weight gain, such as changing food consumption patterns or physical activity habits, but the impact of these changes in reducing excessive weight gain has not been satisfactory.

Limitations of the primary prevention interventions in their ability to reduce excessive weight gain, despite it efficacy in changing behaviors associated with obesity, could be circumvent by combining preventive school activities with family support for those adolescents obese or in risk of obesity. However, to our knowledge there is no study that had tested combining primary prevention at school with secondary prevention. Brazil is internationally recognized for its development of primary health care at the local level. The Family Health Strategy (FHS) Program in Brazil is a model of assistance centered on health teams, which had improved health outcomes in Brazil [11]. As majority of adolescents in Brazil are students from public schools located in areas covered by FHS, it is reasonable to combine primary and secondary prevention in school-based interventions in order to increase the chances of effectiveness in this context.

Thus, the current study presents the rationale and protocol development, pre-tests, and implementation of the trial PAAPPAS, which combine primary prevention activities at school level with secondary prevention at household level to prevent excessive weight gain.

## Methods

### Study design

The trial is a randomized community controlled trial labeled PAAPPAS, which stands for “parents, students, *community health agents* and teachers for healthy eating”. The intervention aimed at reducing excessive weight gain among adolescents combining primary prevention at schools with the primary care health system, through the FHS Program.

Intervention will occur during the school year of 2016 and target fifth and sixth graders from 18 public schools (9 interventions and 9 controls) in the municipality of Duque de Caxias, metropolitan area of Rio de Janeiro, Brazil.

Primary intervention in the school by trained teachers will provide the overall basis for a healthy lifestyle, including food intake, physical activity and sedentary habits. For adolescents diagnosed with excessive weight, household activities will provide additional motivation to change these behaviors. Trained community health agents (CHA) from the FHS Program will visit the families of adolescents with overweight or obesity every month, integrating activities with adolescent and his/her family.

The study will be conducted according to the Consolidated Standards of Reporting Trials (CONSORT) guidelines for cluster-randomized trials [12]. The Ethics Committee of the Institute of Social Medicine (State University of Rio de Janeiro, Brazil) approved the protocol. Written informed consent was obtained from all the participants’ parents.

### Sample size calculation

The sample size for the secondary prevention intervention was estimated based on a standard deviation of body mass index (BMI) equals 3.0; the difference from baseline to the end of intervention among those with overweight and obesity of 1.1 BMI units and the intracluster correlation coefficient was 0.02, according to a previous study conducted in schools [7]. Considering 80 % power and a 5 % significance level, 117 are needed per group to compare intervention with control. In order to reach this sample assuming a prevalence of overweight/obesity of 20 %, the total sample size needed at school is of 2340 participants. Given an intracluster correlation of 0.02, a 2500 sample size was the goal.

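### The scale-up from 117 overweight or obese students per group to 2340 students is unexplained and exactly double the 1170 that the stated inputs give; the step to 2500 does not match school-level clustering

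*Protocol article*

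**What the plan says.** The Sample size calculation section sizes the trial on the secondary prevention comparison, that is, on students with overweight or obesity. Its inputs are a "standard deviation of body mass index (BMI) equals 3.0" and "the difference from baseline to the end of intervention among those with overweight and obesity of 1.1 BMI units". "Considering 80 % power and a 5 % significance level", it concludes that "117 are needed per group to compare intervention with control".

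It then moves from overweight students to all students, "assuming a prevalence of overweight/obesity of 20" per cent, and reports that "the total sample size needed at school is of 2340 participants". Clustering comes last, as a separate step: "Given an intracluster correlation of 0.02, a 2500 sample size was the goal".

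The Study design section gives two arms and "18 public schools (9 interventions and 9 controls"). Under Setting and participants, the school is the randomised unit. No further stratum, group or multiplier is stated between 117 and 2340.

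**The concern.** The paragraph prints its inputs and its result, and the two disagree by a factor of exactly two. The clustering step that follows is much smaller than the school-level design effect implied by the article's own ICC and number of schools. A reader therefore cannot recover from this paragraph what 2500 students in 18 schools can detect. This is the only justification given for the trial's size, and the power it implies will be needed to interpret a null result.

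**Working it through.** **Inputs, all from the protocol article:** SD 3.0, difference 1.1, power 80%, significance 5%, prevalence 20%, ICC 0.02 (Sample size calculation); 9 schools per arm (Study design). The sidedness of the test is not stated; two-sided reproduces the printed 117, one-sided gives 92.

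**Step 1: the per-group figure.** n = 2 × (1.960 + 0.842)² × 3.0² / 1.1² = 116.8, rounded up to 117. The plan's figure is reproduced, with no allowance for clustering.

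**Step 2: the scale-up.** Two groups: 2 × 117 = 234 overweight or obese students. At 20% prevalence: 234 / 0.20 = 1170 students. Printed: 2340. Ratio: 2340 / 1170 = 2.00.

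**Step 3: can a stated input supply the factor of two?**
- Prevalence: 234 / 2340 = 10% would be needed. The section says 20%. The 24% cited under Setting and participants would lower the total to 234 / 0.24 = 975.
- Power or sidedness: 90% power (157 per group) gives 1570; a one-sided test (92 per group) gives 920.
- Clustering: a design effect of 2 at ICC 0.02 needs 1 + (2 − 1)/0.02 = 51 analysed students per cluster. At 2340 students there are 468/18 = 26 overweight students per school, and the design effect is 1 + 25 × 0.02 = 1.50. The text also applies the ICC after 2340, not before it.

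**Step 4: the clustering step as printed.** 2500 / 2340 = 1.068. At ICC 0.02 this implies 1 + 0.068/0.02 ≈ 4.4 analysed students per cluster. At 2500 students there are 500 overweight students, or 500/18 = 27.8 per school, and the school-level design effect is 1 + 26.8 × 0.02 = 1.536.

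**Step 5: total for 80% power with 9 equal schools per arm.**
- Normal approximation: n = n₀(1 − ICC)/(1 − n₀ × ICC/9) with n₀ = 116.76, so 114.42/0.7405 = 154.5 per arm; total 2 × 154.5/0.20 = 1545 students.
- t with 16 df (18 schools − 2), solved numerically: 184.1 per arm (20.5 per school, design effect 1.389, effective n 132.5, SE 0.3685, noncentrality 2.985, power 0.800); total about 1841 students.

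**Step 6: power for 1.1 units, 20% prevalence, equal school sizes.** SE = 3.0 × √(2/effective n).

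| Students | Overweight per arm | Design effect | Effective n per arm | SE | 1.1/SE | Power, t (16 df) | Power, normal |
|---|---|---|---|---|---|---|---|
| 1170 | 117 | 1.240 | 94.4 | 0.437 | 2.52 | 66% | 71% |
| 2340 | 234 | 1.500 | 156.0 | 0.340 | 3.24 | 86% | 90% |
| 2500 | 250 | 1.536 | 162.8 | 0.333 | 3.31 | 87% | 91% |

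**Step 7: unequal schools.** The article gives no school sizes. Taking a coefficient of variation (CV) of 0.5 to 0.7 as an assumed range, with design effect 1 + ((1 + CV²) × 27.8 − 1) × 0.02, the design effect at 2500 is 1.674 to 1.808 and power (t, 16 df) is about 84% to 82%.

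**The case against.** The strongest reply is that nothing in the trial is harmed. The statistical core, 117 per group, follows from its inputs. The text calls 2500 a goal and nowhere claims that it yields exactly 80% power, and a goal above the minimum is no fault. Under the article's own SD and ICC the trial is more than adequately sized for 1.1 units. All of this stands. It limits the consequence but does not reconcile the printed figures.

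The factor of two might be a deliberate but unreported allowance, for example for non-consent. That is possible, and it is why the fix leaves room to name a source. It is tempting to say that the doubling for two groups was made twice, since 4 × 117/0.20 = 2340. The article does not show this: 10% prevalence or an unstated allowance gives the same number.

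The 1.068 might be a class-level design effect, since the Statistical analysis section clusters on classes and about 4.4 overweight students per class would mean classes of about 22 at 20% prevalence. That is plausible as an origin. It does not make the step sufficient, because schools were randomised and students within a school share the allocation.

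Four stronger readings are not supported:
- *The trial is underpowered for 1.1 units.* The error runs the other way.
- *1170 students would have been enough.* That figure carries no clustering, and its power falls to about 66–71% once clustering is included.
- *The article should have stated an attrition allowance.* A condensed article may leave that to the full protocol.
- *2500 leaves general slack.* The power above is for the overweight subgroup only. The Outcomes section also names a 0.4-unit target for mean BMI at the primary prevention level, which this calculation does not address.

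**Conclusion.** The point holds for the scale-up and the clustering step, not for the per-group figure. From the stated inputs the unclustered total is 1170, and the printed 2340 is exactly double without a stated reason. The inflation to 2500 (1.068) is well short of the school-level design effect (about 1.54).

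The two discrepancies act in opposite directions, and the net result is conservative. Against a clustered requirement of about 1545 (normal) to 1841 (t, 16 df), 2500 students give about 91% and 87% power respectively for 1.1 units. This rests on SD 3.0, ICC 0.02 applied at school level, 20% prevalence and equal school sizes; with the assumed variation in school size, power by t is about 82–84%. It is a wrong stated sample size that needs correcting, but it does not threaten the secondary prevention comparison.

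**What to change.** Rewrite the one paragraph in Sample size calculation:

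1. Keep 117 per group and state that it is two-sided and before clustering.
2. Replace 2340 with 1170 before clustering, or state where the factor of two comes from.
3. Show the school-level design effect, with 18 schools and ICC 0.02, and the resulting total for 80% power: about 1545 students (normal) to 1841 (t, 16 df).
4. Restate what 2500 students provide: about 87% (t, 16 df) to 91% (normal) power for 1.1 units in the overweight or obese subgroup, assuming equal school sizes and 20% prevalence. Replace the equal-size assumption with the actual school sizes, which the investigators hold.
5. Say that this figure covers the secondary prevention comparison only and not the 0.4-unit target, and do not present 1170 as a recruitment target.

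The cost is one corrected paragraph. Recruitment, allocation and analysis are unchanged.

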### Setting and participants

This study takes place in the municipality of Duque de Caxias (population, 842,686) [13], located 27 km from the state capital and is part of the metropolitan area of Rio de Janeiro. It is one of the poorest areas in the state of Rio de Janeiro, and the prevalence of obesity in this region is rapidly increasing among adults and adolescents [3, 4]. A population based study carried out in Duque de Caxias revealed a mild family food insecurity prevalence of 36 %, and a prevalence of overweight/obesity among adolescents of 24 % [3]. For this study, two of four districts in Duque de Caxias were included, and from 45 municipal schools, 18 schools with fifth and sixth grades classes were selected. All students enrolled in the 5th and 6th grades of selected schools are eligible for this study. The exclusion criteria are students with physical disabilities and pregnant adolescents (Fig. 1).

**Fig. 1 Fig1:**
[figure not shown]
Study design

Schools were randomized half in the control group and half in the intervention group based on number of students using opaque envelopes, in the presence of investigators not involved in the current study. Schools will remain in their allocated group for the duration of the study. Participants in the control arm will receive only the routine activities for healthy behaviour of the school.

### Intervention

The primary prevention at school was based on literature review of eating behaviors, environmental factors associated with obesity [7] and pilot studies. The foods targets were the most important contributors to energy intake identified in the more recent Brazilian survey [14]. The intervention focus on encouraging students to change eating habits and food consumption and encouraging them to increase physical activity and reducing sedentary behavior. Teachers are trained, and every month they receive material for 1-h session of in-class activities (Table 1), except for the first one when students prepare salads. To reinforce the in-class messages, booklets, recipes, and flyers are sent to the families.

**Table 1 Tab1:** Intervention components, description, dose and expected behavior change

Intervention components	Description	Dose per month	Expected behavior change
School			
1) Healthy eating	Definition of healthy eating and food choices using two educational games.	2 × 30 min	To improve the choices when eating and purchasing foods at supermarkets and fairs.
	Main message: reduction of cookies, sodas, and sugar-sweetened beverages.		
2) Culinary classes	First activity- students assemble salads at school choosing from a large variety of greens and fruits. In the second, they prepare vegetarian pizzas.	1 × 50 min	To develop cooking skills increasing healthy eating choices, to discuss sensory aspects of food and to stimulate teamwork.
3) Water exchange with sugar sweetened beverage	Measuring the amount of sugar in different drinks. Sugar intake and prevention of diseases.	2 × 30 min	To increase water consumption.
	A squeeze with the PAAPPAS logo will be provide to the students and teachers.		To develop a critical view about the consumption of sugar sweetened beverages.
4) Physical activity and sedentary behavior	How many Olympic games they have heard of. What exercises they do and would like to do. Class games related to the Olympic games and time spend sedentary.	2 × 30 min	To stimulate exercise.
5) Fruit consumption	Group discussion and games about of fruits. What they like and dislike. Diversity of fruits from Brazil. How buy fruit al affordable prices and the importance of eating fruits.	2 × 30 min	To exchange cookies consumption by fruit.
6) Mindful eating and self-control strategies	Activity regarding hunger and satiety cues; how to combine foods to make a healthy dishes.	2 × 30 min	To develop eating awareness regarding hunger and satiety physiological signs. To facilitate choices of healthy dishes.
Household	CHA activities		
1) Health eating habits and anthropometry	Measure weight and waist of the adolescent and mother.	30 min	To improve eating habits.
	Encourage adolescents and family to: 1) Keep regular mealtimes; 2) Eat with the family at the table; 3) No television, computer or mobile phone during meals; 4) Eating meal slowly (about 20 min); 5) Serve the dish once, except for vegetables.		
2) Reduce soft drinks and sugar sweetened juices	Show pictures of the amount of sugar in sodas and popular drinks negotiating reduction strategies: 1) Avoiding buying; 2) Replace soft drinks and juices by water and flavored waters; 3) Facilitate adolescent access to fruits; 4) Buy season fruits.	20 min	To reduce soft drinks and sweetened juices and prompt specific strategies to achieve this target.
3) Physical activity and sedentary behavior	Discuss that lifestyle modification are strong allies to lose weight. Provide a list of facilities free of charge in the neighborhood with physical activities such as churches and NGOs. Sedentary reduction strategies: 1) Reduce one hour time in computer games and TV; 2) Encourage the use of physical activity mobile app. 3) Encourage standing or walk during the interval of TV programs or in the game phase shift.	20 min	To increase physical activity and reduce sedentary behavior.
4) Biscuits and sweets	How to read nutritional labels using as example cookies, candy and other high sugar products. Negotiate: 1) Reducing intake of cookies, biscuits and sweets and also avoiding buying them; 2) Replace cookies with homemade popcorn, fresh coconut; peanuts and corn; 3) Substitute processed sweets, with homemade marmalades and jams low in sugar; 4) Add milk to coffee to reduce sugar.	20 min	To reduce biscuits and sweets consumption and prompt specific strategies to achieve this target.
5) Industrialized products	Identify dyes, preservatives and flavor enhance substances in labels avoid buying those high-energy industrialized products. Stimulate: 1) Replacement of noodles; processed sausage and hamburger for homemade burger /ground beef /egg; 2) Clean salads and vegetables in advance for consumption during the week (ask adolescent for help); 3) Keep always in the refrigerator fresh or frozen vegetables and beans; 4) Use spices and make attractive and colorful raw salads and vegetables. 5) Make shopping list to avoid buying unnecessary foods.	20 min	Provide information to reduce the consumption of industrialized products and prompt specific strategies to achieve this target.

Activities for secondary prevention at households, as indicated in Table 1, were based on Paulo Freire’s theory [15]. Secondary prevention is coordinated by the Health Secretary of the Municipality of Duque de Caxias and will be carried out from June to December by the CHA. The CHA will encourage lifestyle changes at family level. The goals are the same as those of the primary prevention with emphasis on eating behaviors and food consumption (reducing soda and sugar sweetened beverages, cookies, sweets, and processed food and increasing fresh foods) and on stimulating the increasing of physical activity and reducing sedentary habits. It also includes clues to reduce total energy intake by families. Each month the adolescent and his/her family are stimulated to choose one of the five goals (Items 1 to 5 in Table 1).

This is the first time that CHA are trained to address obesity at the family level. Goals and all material used in the intervention were developed in partnership with Health and Education authorities in the municipality of Duque de Caxias (Rio de Janeiro, Brazil).

### Outcomes

At the primary prevention level we are testing a reduction of 0.4 units of mean BMI and for the secondary prevention program a reduction of 1.1 units of BMI is expected. Secondary outcomes include body fat and waist circumference. Many behavior changes evaluated will allow measure the adherence to the intervention.

### Data collection at school

Anthropometric measures, food consumption and a questionnaire are being collected at baseline [March-April] and post-intervention [November-December] using personal digital assistant (PDA). Students will complete a structured questionnaire under the supervision of field researchers using PDA and the CHA will take anthropometric measurements.

Food consumption will be assessed by 24-h recall and a short (23 items) food frequency questionnaire (FFQ), which is a reduced version of an FFQ validated for adolescents of Rio de Janeiro [16]. The 24-h recall will use the BrasilNutri software, entering data during interviews in schools. The software encompasses a computerized food database developed for the 2008-2009 nationwide dietary survey [17].

Measurement of physical activity will include the evaluation of exercise, leisure activities, commuting to school, and sedentary activities (video games, television and computer time) measured by questionnaire [18] and in a subgroup by accelerometer (GT3X Actigraph).

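### The cadre that makes the home visits also takes the final anthropometry, and nothing keeps an agent from measuring students he or she has visited

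*Protocol article*

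**What the plan says.** The points below are from the protocol article.

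- **Who measures.** Under Data collection at school: "Students will complete a structured questionnaire under the supervision of field researchers using PDA", and "the CHA will take anthropometric measurements".
- **When.** The same section says that the anthropometric, dietary and questionnaire data "are being collected at baseline [March-April] and post-intervention [November-December".
- **Who delivers the household programme.** Under Study design, trained CHA "will visit the families of adolescents with overweight or obesity every month". Under Intervention, this secondary prevention "will be carried out from June to December by the CHA".
- **Who receives it.** The Abstract limits it to one arm: "those from the intervention group who are overweight or obese will be followed monthly at home by community health agents".
- **What happens at home.** The first household item in Table 1 is "Measure weight and waist of the adolescent and mother".
- **What is judged.** Under Outcomes, for primary prevention "we are testing a reduction of 0.4 units of mean BMI", and 1.1 BMI units are expected for secondary prevention. Waist circumference and body fat are secondary outcomes.
- **Safeguards stated.** Anthropometric and body composition refers to standardised procedures. Setting and participants describes opaque envelopes and outside investigators at the draw, which protect allocation and not measurement. The article does not mask the measurers or separate them from the agents who visit.

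**The concern.** The article gives one cadre both the delivery of the secondary-prevention programme and the recording of its endpoint. An agent who has visited a family for months knows that the student is in the intervention arm and may remember the weights and waists read at home. The cadre also has an interest in the result: the Discussion says that a positive finding would lead to all CHA in the municipality being trained in the programme.

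Control families receive no visits, so no control student can be measured by his or her own visitor. If agents favour their own students even slightly, the error differs by arm. The mixed model cannot separate such an error from a treatment effect, and more students would not shrink it. Most exposed are BMI in the overweight/obese comparison and waist circumference. A scale display leaves little room for judgement, whereas height and waist depend on how the operator positions the student and reads the instrument.

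**Working it through.** **1. Timing and roles side by side**

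| Activity | Who | When |
|---|---|---|
| Baseline anthropometry | CHA | March-April |
| Home visits, intervention arm only | CHA | June-December |
| Final anthropometry | CHA | November-December |

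Baseline precedes every visit, and the final wave overlaps the last months of visiting. The exposed measurement is therefore the final one.

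**2. The plan's own figure**

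Inputs from Sample size calculation: SD 3.0, difference 1.1, 80% power, 5% significance. With a two-sided test,

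n = 2 × (1.960 + 0.842)² × (3.0/1.1)² = 15.70 × 7.438 = 116.8, so 117 per group.

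This reproduces the stated 117. The concern does not depend on it, but step 5 uses the same SD and n.

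**3. Shift in a visited student**

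The documents give no measurement-error figures, so body sizes and errors here are assumptions. For a student of 42 kg and 1.45 m, read 0.5 kg too light and 0.5 cm too tall at the final wave only:

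- true BMI: 42/1.45² = 19.98
- recorded BMI: 41.5/1.455² = 19.60
- shift: 0.37 units, of which weight alone gives 0.24 and height alone 0.14 (parts rounded separately)
- share of the 1.1-unit target: 0.37/1.1 = 34%

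Range over two other assumed body sizes:

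| Error | 40 kg, 1.45 m | 55 kg, 1.48 m |
|---|---|---|
| Height +0.5 cm | 0.13 | 0.17 |
| Height +1.0 cm | 0.26 | 0.34 |
| Weight −0.5 kg | 0.24 | 0.23 |
| Weight −0.5 kg and height +0.5 cm | 0.37 | 0.40 |

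If only height is misread, by 0.5 cm, the shift is 0.13 to 0.17 units, or 12% to 15% of 1.1.

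**4. Shift averaged over all students**

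Only overweight or obese students are visited. Sample size calculation assumes 20% of students; Setting and participants reports 24% from a local survey. If the error is confined to them:

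- 0.20 × 0.37 = 0.07 units, about 19% of the 0.4-unit target
- 0.24 × 0.37 = 0.09 units, about 22% of it

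**5. Effect on the error rate**

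With no true effect and a bias b, the chance of a significant result is 1 − Φ(1.96 − b/SE) + Φ(−1.96 − b/SE).

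- Overweight/obese comparison, 117 per group, no clustering: SE = 3.0 × √(2/117) = 0.39. The nominal 5% becomes 5.7% at b = 0.1, 8.0% at 0.2, 11.9% at 0.3 and 17.5% at 0.4. A bias of 0.37 lies between the last two. Allowing for clustering would widen the SE and lower these figures.
- All students, 1250 per group, 18 schools, intracluster correlation 0.02: design effect = 1 + (2500/18 − 1) × 0.02 = 3.76, and SE = 3.0 × √(2 × 3.76/1250) = 0.23. At b = 0.1 the rate is 7.1%, so a bias of 0.07 to 0.09 gives less than that.

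**The case against.** The strongest defence is that the article names a role, not individuals. A reader might infer that the intervention arm is measured by the very people who delivered the programme. The text does not say so, and it does not say who measures in control schools. If CHA measure in all 18 schools, the type of measurer is the same in both arms and what remains is knowledge of allocation. This limits the point to a risk. It does not remove it, because the article states the overlap of roles and nothing separates the two tasks. The Discussion also has each agent working in the territory to which he or she is affiliated, which makes overlap plausible.

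A reader might also infer that baseline readings could tilt who is classified as overweight. The documents do not support this: baseline comes before any visit, the order of randomisation and baseline measurement is not stated, and no motive or direction of error is evident.

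A third tempting reading sets 0.37 against the 0.4-unit target and concludes that measurement error could account for nearly all of it. That needs both errors, in the favourable direction, in every intervention student, including the roughly 80% whom no agent visits. It also needs them at the final wave only, since an error constant across both waves largely cancels in a longitudinal analysis. Confined to visited students, the shift is about 0.07.

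Standardised procedures do limit the error, especially for weight. They do not mask the measurer. Measurer training and assignment may well be set out in a fuller protocol, and their absence from an article is not the point here. The point is the assignment that the article states.

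**Conclusion.** The point stands as a design choice that carries an avoidable risk. As written, CHA may take the final BMI and waist of students they have visited and whose arm they know, with no counterpart in the control arm. The exposure is mainly in the overweight/obese comparison, and in height and waist more than in weight.

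The documents do not give the size of any bias. Under the assumed 0.5 kg plus 0.5 cm error at the final wave, it is about 0.37 BMI units in visited students, a third of the 1.1-unit target. Averaged over all students it is about 0.07 units, if the error is confined to the 20% who are visited. Both figures assume that every visited student is misread by that amount in the same direction, so they illustrate scale and are not estimates. The documents do not show that such bias has occurred or will occur. This is a cheap improvement to make before the final wave, and not a defect that by itself invalidates the trial.

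**What to change.** For the November-December wave:

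- Assign each CHA to measure only at schools whose families he or she does not visit.
- Have the same measuring teams cover both intervention and control schools.
- As far as possible, keep home-visit readings from the measurers.
- Record who measured which student, so that measurer effects can be examined.

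Alternatively, field researchers who do not deliver the intervention could take the measurements, if their workload allows. The article states neither their independence nor their spare time, and 24-hour recall interviews also take place at school. The questionnaire should not pass to CHA in exchange: it is self-reported, it informs the assessment of adherence, and it is more open to the influence of an interested interviewer than a scale or stadiometer.

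The cost of the first option is some scheduling and travel. It needs no extra staff and no change in sample size. Baseline collection is described as already under way, so the change is aimed at the final wave.
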